**Methods:**

The present study is a two-phase randomized controlled trial. *Phase 1* will involve (1) an iterative design process to develop the online yoga prescription for phase 2 and (2) qualitative interviews to identify cultural barriers to recruitment in non-Caucasian women (i.e., predominately Hispanic and/or African American) who have experienced stillbirth (*N* = 5). *Phase 2* is a three-group randomized feasibility trial with assessments at baseline, and at 12 and 20 weeks post-intervention. Ninety women who have experienced a stillbirth within 6 weeks to 24 months will be randomized into one of the following three arms for 12 weeks: (1) intervention low dose (LD) = 60 min/week online-streaming yoga (*n* = 30), (2) intervention moderate dose (MD) = 150 min/week online-streaming yoga (*n* = 30), or (3) stretch and tone control (STC) group = 60 min/week of stretching/toning exercises (*n* = 30).

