**Fig. 1 Fig1:**
[figure not shown]
Study flow chart: the *left side* of the diagram illustrates the flow of the study for phase 1, and the *right side* illustrates the phase 2

#### Phase 1

Part A. Iterative design: We will develop the yoga prescription using an iterative design process with the following steps:Identify 30 videos from the existing UDAYA (an online-streaming commercial yoga website; https://udaya.com) library.Gather a panel of women whose babies were stillborn (*n* = 5) and a panel of women who are regular yoga practitioners and have not experienced a baby’s death (*n* = 5) to review (i.e., watch or engage) yoga videos selected from step one above.Develop (produced by Udaya.com) up to 12, 30-min yoga videos specifically for the grieving mothers.

Part B. Interviews to identify cultural barriers to recruitment: We will recruit five non-Caucasian (predominately Hispanic and/or African American) women who have experienced stillbirth to participate in a 15–20 min phone interview. These interviews will guide the recruitment process for phase 2, and additional recruitment materials will be developed to ensure adequate enrollment of non-Caucasian women in the study. The interview questions will consist of questions related to:Perceptions/opinions about yoga related to physical and mental health.Strategies to ensure adequate enrollment and retention of non-Caucasian women to participate in a yoga intervention.

#### Phase 2

Phase 2 is a three-group randomized feasibility trial with assessments at baseline and at 12 and 20 weeks from baseline. After completion of the consent process and the baseline assessment, 90 women will be randomized into one of the following three arms for 12 weeks: (1) intervention low dose (LD) = 60 min/week yoga (*n* = 30), (2) intervention moderate dose (MD) = 150 min/week yoga (*n* = 30), or (3) stretch and tone control (STC) group = 60 min/week of stretching/toning exercises (*n* = 30).

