##### Low and moderate dose intervention groups

The low and moderate dose intervention groups will be asked to follow a 12-week online yoga prescription (for 60 and 150 min/week, respectively). We selected the low dose of 60 min/week because this is the minimal amount needed to experience mental and/or physical health benefits [40, 52–55]. We chose the moderate dose of 150 min/week because this reflects the physical activity guidelines [56].

The style of the online yoga videos will be Hatha because (1) Hatha combines a physical practice with a meditative component to cultivate mindfulness (i.e., moment to moment, non-judgmental awareness, cultivated by paying attention in a specific way) [57] and self-awareness and (2) includes instruction from a variety of lineages (e.g., Iyengar, Asthanga, Vinyasa). The online prescription assures the poses used are identical for both intervention groups. Participants will be asked to complete the yoga videos in a specific order, which will include specialized preparatory instructions for each video to ensure comfort and safety [56].

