##### Stretch and tone control group

The STC group will be asked to follow a 12-week online stretching/toning exercise prescription for 60 min/week to match minimal dose of intervention group (i.e., LD). We will develop 12, 30-min videos for the STC group prescription (produced and filmed by UDAYA). The STC videos will be adapted from an already existing, well-established, evidence-based control condition (originally designed for older adults in other funded trials) to be specific for women who are underactive (<150 min of moderate activity per week) [47–49, 58, 59]. The instructor will begin and end each class with a 3-min warm-up/cooldown. The instructor will ask participants to perform each isolated stretch or toning exercise for 1–2 sets (20–45 s or between 10 and 15 repetitions). Participants will be asked to perform slow, controlled, and complete movements. Progression will include demonstration by the instructor of modifications with a slightly less difficult and a more challenging version for the specific exercise. For example, a participant may be asked to perform a plank on their knees and a modification may be to straighten their legs, making the exercise more difficult. Variability will be demonstrated by changing the stretching and toning exercises every 3 weeks. For example, in the first 3 weeks, participants will be introduced to the new activities, and in the remaining weeks 4 to 12, they are encouraged to increase the difficulty by adding more repetition or performing the more challenging modification. Participants will be asked to complete the STC videos in a specific order, which will include a warm-up, four upper body, four lower body, three trunk/core, and one to two balance exercises, with appropriate progression over 12 weeks. The STC videos will have discussion related to form and safety by the instructor (i.e., no guidance for movement with breath or mindfulness). Additionally, videos will have students in the background following instructor cues and demonstrating variations of exercises. There will be no final relaxation pose in the STC videos (i.e., the rest period after completion of a yoga class).

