##### Procedures

UDAYA will provide the research team with 90 membership accounts pre-paid for the length of the study that will have access only to the videos specific to the participants group assignment (i.e., participants will not have access to the full UDAYA video library). The research staff will assign UDAYA membership accounts to all participants (i.e., intervention and control) upon enrollment into the study and will provide them with a username and password to access UDAYA prior to their participation in the study. In addition, participants will be asked to wear an accelerometer (i.e., GENEActiv) to measure physical activity and sleep quality for 1 week at baseline, post-intervention (12 weeks from baseline), and follow-up (20 weeks from baseline) and complete assessments at these time points.

Participation in the videos (intervention and control groups) will be automatically tracked (class taken, time of day, length of use, and etc.) via web analytics software throughout the study in each group. Research personnel will send weekly reminders (email or text message) to participants for minimal dose compliance. Additionally, the research team will send each participant a Qualtrics link to report (1) completion of sessions, (2) rating of perceived exertion, (3) assessment of mindfulness, (4) other physical activity participation, (5) pregnancy status, mental health, use of psychiatric medication, and adverse events. Participants will be asked weekly about participation in support groups or individual/group-based counseling sessions. Participants will be discouraged from attending face-to-face yoga/stretching/toning classes during the study.

In the case that a woman becomes pregnant during the study, she will be asked to complete the Physical Activity Readiness Medical Examination for Pregnancy (PARmed-X for Pregnancy), a health screening tool completed with the health care provider to ensure it is safe for women to participate in prenatal exercise. We will also send women a pregnancy safety handout (specific to yoga or general physical activity depending on group assignment) for their review.

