Eligible participants (see Table 2 for eligibility criteria) will be asked to complete a phone intake appointment, an electronic informed consent, a HIPAA authorization form, and baseline assessments of self-report measures (see Table 3). Participants will then be randomized to an intervention (LD or MD) or control group. The research team will mail intervention group participants: (1) a packet with study info and directions, (2) a document including strategies to overcome barriers to online yoga participation, (3) an accelerometer (GENEActiv) with instructions on how to wear, and (4) a yoga mat, two blocks, and a strap. The control group will receive (1) a packet with study info and directions, (2) a document including strategies to overcome barriers to online physical activity participation, (2) an accelerometer (GENEActiv) with instructions on how to wear and a pre-paid return mailer, and (3) a stretching mat and band. All participants will be asked to begin wearing the GENEActiv immediately upon receiving it for one full week and then mail monitor back in a pre-paid envelope supplied in their packet. The GENEActiv will be mailed to participants again at post-intervention (12 weeks from baseline) and follow-up (20 weeks from baseline) using the same process. When participants have worn the GENEActiv for 1 week, they will be emailed their UDAYA username and password to begin accessing their respective videos.

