At 6 weeks (midway through the intervention), participants will be asked to complete the IES-R and answer a 1-item Likert-based question related to whether they think the intervention is contributing to their symptoms for the IMC to review. Every 2 weeks of the intervention, participants will be asked to fill out the PHQ-9 via Qualtrics within 48 h. A research team member will monitor PHQ-9 completion daily (including weekend/holidays). Women with scores suggestive of clinical depression (>15) will be notified and advised to follow up with their primary care physician. If suicidal ideation is noted with a screen score of two or three on question 9 of the PHQ-9, the participant will be contacted within 24 h by a crisis-trained, clinical staff for further assessment of risk. Clinical providers trained by the MISS Foundation are well equipped to handle psychological crises, have a system currently used for their existing 3000 grieving families they help annually, and have staff available on weekends/holidays. If imminent suicidal risk is present, the staff will follow MISS Foundation emergency procedures to ensure participant safety, and the participant will be discontinued from the study. If there are no concerns for active suicidal risk after the phone assessment, the participant will be able to continue in the study if she desires. All participants will have the MISS Foundation provider’s phone number, and the research personnel can either email, call, text, or page the lead clinical provider to respond to psychiatric issues. Depending on the need of the participant, one of them will be able to talk to a clinician within 2 to 3 h.

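### On the plain reading of the enrolment sequence, the post-intervention questionnaires fall at least one week before the 12-week programme ends; day 0 is undefined and the abstract's timing contradicts the body

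*Protocol article*

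**What the plan says.** **Length of the programme.** Each yoga arm "will be asked to follow a 12-week online yoga prescription", and the control arm "will be asked to follow a 12-week online stretching/toning exercise prescription" (sections on the low and moderate dose groups and on the stretch and tone control group).

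**Assessment dates.** Study design, Phase 2, gives "assessments at baseline and at 12 and 20 weeks from baseline". Procedures has the accelerometer worn "for 1 week at baseline, post-intervention (12 weeks from baseline), and follow-up (20 weeks from baseline"), so it treats post-intervention and week 12 from baseline as the same date. Study enrollment does likewise. Table 3 puts the satisfaction survey, the first interview and the post-intervention questionnaires in its 12-week column. The abstract instead gives "assessments at baseline, and at 12 and 20 weeks post-intervention".

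**Order of events.** Study design and Study enrollment both place the self-report baseline before randomisation. Study enrollment then mails the accelerometer, asks for a full week of wear from receipt, and continues: "When participants have worn the GENEActiv for 1 week, they will be emailed their UDAYA username and password to begin accessing their respective videos".

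**Other login times.** Allocation puts the username and password in the packet emailed after randomisation and mentions no wear week. Procedures assigns the accounts at enrolment and supplies the login details before participation starts.

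**Baseline.** The accelerometer week is itself listed as a baseline measure (Procedures, Table 3). No section names the day from which the 12 and 20 weeks are counted.

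**The concern.** If baseline means the questionnaires completed before randomisation, the programme cannot start on that day. A parcel must arrive and a week of wear must pass first. A 12-week programme that starts late cannot be finished 12 weeks after baseline.

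Three things would be affected.

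- **IES-R.** PTSD symptoms are the primary outcome of the preliminary-effects aim. They would be read while women are still in the programme.
- **Satisfaction survey and interviews.** The survey feeds the 70% benchmarks. The section on feasibility measures describes it as an end-of-intervention survey, but it would be answered before the end.
- **Follow-up.** The time from programme end to the 20-week assessment would be shorter than the schedule suggests and would differ from woman to woman.

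The abstract adds a separate contradiction. Read literally, it puts both later assessments well after the programme has ended.

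**Working it through.** This is timeline arithmetic.

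**Inputs**
- Programme length: 12 weeks (intervention sections).
- Wear week before the login: 1 week (Study enrollment).
- Assessments: weeks 12 and 20 from baseline (Study design, Procedures, Study enrollment).
- *m*: weeks from the self-report baseline to receipt of the device. The document does not give this; 0 to 2 weeks is assumed.

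**The plan's own equation.** The plan equates week 12 with post-intervention. This reproduces exactly if baseline is counted from the end of the wear week. It reproduces approximately if the login is sent at randomisation and randomisation follows baseline at once.

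**Plain reading: count from the self-report baseline, login after the wear week**
- Delay to first access: L = m + 1
- Programme weeks done at week 12: 12 − L
- Programme end, in weeks from baseline: 12 + L
- Programme end to week 20: 20 − (12 + L) = 8 − L

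| m | L | Weeks done at week 12 | Programme ends | Gap to week 20 | Prescribed minutes available: 60-min arms (of 720) / 150-min arm (of 1,800) |
|---|---|---|---|---|---|
| 0 | 1 | 11 (92%) | week 13 | 7 weeks | 660 / 1,650 |
| 5 days | 1.7 | 10.3 (86%) | week 13.7 | 6.3 weeks | 617 / 1,543 |
| 1 week | 2 | 10 (83%) | week 14 | 6 weeks | 600 / 1,500 |
| 2 weeks | 3 | 9 (75%) | week 15 | 5 weeks | 540 / 1,350 |

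The first row needs no mailing assumption: the wear week alone leaves one programme week undone.

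**Other anchors**
- Start of the wear week: 12 − 1 = 11 weeks done.
- End of the wear week: 12 weeks done, with 8 weeks to week 20. The IES-R change would then span 12 + 1 + m = 13 weeks or more from the self-report baseline.
- Login at randomisation (Allocation): about 12 weeks done. The device is mailed only after randomisation, however, so the baseline accelerometer week could overlap the programme.

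**Accelerometer at week 12.** The device is mailed at week 12 by the same process. With the same mailing time it is worn from week 12 + m to week 13 + m. On the plain reading the programme ends at week 13 + m, so this wear covers the last programme week.

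**Abstract read literally.** The assessments fall 12 + 12 = 24 and 12 + 20 = 32 weeks after the programme starts. Thirty-two weeks is about 7.4 months. For a woman enrolled at the end of month 20, that is 20 + 7.4 = month 27.4 before any mailing or wear time. Table 5 ends follow-up collection at month 26.

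**The case against.** The strongest reply is that baseline may be a period rather than a day. Procedures and Table 3 count the accelerometer week as baseline. Table 5 runs baseline collection through months 21–22, after recruitment ends in months 19–20. If the clock starts when the wear week ends, week 12 is programme end and nothing is lost. This stands as a possible reading, and it is why the shortfall cannot be stated as certain. It does not settle the text, because no section says so and Study enrollment gives the name baseline to the questionnaires completed before randomisation.

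A reader might infer several stronger things that the document does not support:

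- **That video access certainly opens only after the wear week.** Allocation and Procedures give other times. The demonstrable fault is that the three sections disagree.
- **That the post-intervention accelerometry is taken 1 to 2 weeks early.** The device is mailed at week 12, so it is worn later.
- **That the attendance benchmark of nine of 12 weeks is cut short.** Web tracking runs throughout the study, and nothing closes the count on the day of the survey.
- **That the six-week safety check runs on a conflicting clock.** "At 6 weeks (midway through the intervention), participants will be asked to complete the IES-R" is simply half of 12 weeks and fits a clock that starts with the programme.
- **That an eight-week post-treatment interval is promised and broken.** The document promises only week 20 from baseline; eight weeks is an inference.
- **That the comparison between arms is biased.** The delay applies to all three arms alike.

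It is also fair to say that this is a feasibility trial whose PTSD aim is exploratory, and that exact visit anchors may sit in the full protocol or the manual of procedures. That lowers the weight of the point. It does not remove contradictions printed in the article itself.

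**Conclusion.** The point holds as a timing conflict that should be fixed, with moderate confidence. On the plain reading of Study design and Study enrollment, the 12-week questionnaires, satisfaction survey and interviews are taken with at least one programme week left. The shortfall is one week with no mailing time and two weeks with one week of mail. The interval from programme end to week 20 is 7 weeks at most.

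The one-week minimum rests on counting from the self-report baseline and on the login sequence in Study enrollment. Anything beyond it rests on an assumed mailing time. The shortfall disappears if baseline means the end of the wear week.

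Two contradictions need no assumption: the abstract against the body on assessment timing, and Study enrollment against Allocation and Procedures on login release.

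The consequence is a blurred meaning of post-intervention and of follow-up, with an interval that varies with the post. It is not, by itself, bias between the arms.

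**What to change.** 1. Reconcile Procedures, Study enrollment and Allocation so that the login is released after the baseline wear week in all three. This also keeps programme exercise out of the baseline accelerometer reading.
2. Define day 0 as the date of login release.
3. Count the 6-, 12- and 20-week assessments, the satisfaction survey and the 12-week attendance window from day 0.
4. Correct the abstract to say 12 and 20 weeks from the start of the intervention.

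**Effect.** In weeks from the self-report baseline, the two later assessments move to 13 and 21 (m = 0), 14 and 22 (m = 1) or 15 and 23 (m = 2). They then fall at programme end and eight weeks later. The baseline IES-R still precedes day 0 by 1 + m weeks, because it is rightly taken before randomisation.

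**Cost.** Only protocol wording and survey-trigger dates change, but the last visits move later by the wear week plus mailing time, so Table 5 should be checked. For a baseline at the end of month 20, week 20 (about 4.6 months) plus a two-week shift (about 0.5) gives month 25.1, inside the follow-up window that ends at month 26. Table 5 also allows baseline collection through month 22. A baseline at the end of that month gives 22 + 4.6 = month 26.6 before any shift and about month 27.1 after it. The follow-up window may therefore need extending for the last women enrolled.

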### Confirming participants’ identity/eligibility

During the intake phone call, we will confirm the participant’s identity and eligibility with the following:Confirmation of answers from the eligibility screener (i.e., date of the stillbirth delivery, cause if known, location of death).A small sample of women (~30%; *N* = 27) will be asked to verify information about their baby’s death to confirm their eligibility based on stillbirth history. All women will be asked to sign a HIPAA authorization form at the same time in which they sign their informed consent (in the case where they are randomly selected for research staff to obtain medical records related to the death of their baby). As women enter the study and are assigned an ID, those with an ID that matches one contained in a random number table generated prior to recruitment into the study will be selected.The research team will request the records (e.g., date, gestational age, birthweight, and Apgar scores). If there is a significant number of women who are ineligible (>30%), we will increase the number that we confirm eligibility to ~40% using medical records.

### Allocation (phase 2 only)

Block randomization will be used to assign participants to treatment groups. Specifically, the biostatistician will construct 15 blocks of six participants using SAS PROC PLAN with a random number seed known only by the biostatistician. This will be done at the beginning of the study (front-loaded) and provided to a research staff member not associated with this study (i.e., trusted broker). The trusted broker will utilize the treatment allocations to sequentially assign enrollees to randomized treatment groups (the biostatistician will be shielded from enrollment date and enrollment order, and participant IDs will not reflect enrollment order). The trusted broker will hold the codes that match participants to treatment groups. Research staff members will call the trusted broker to determine assignment to group. In case of adverse events (AE), the research staff member will call the trusted broker to provide for unblinding (AE only). After randomization, participants will be emailed a study information packet (i.e., instructions, UDAYA username/password) according to the intervention assigned. The initiation of the study will begin after allocation to study arm (see Fig. 2 for phase 2 study flow chart).

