##### Feasibility (acceptability, demand, and practicality)

We will utilize Bowen and colleagues’ [60] standards for feasibility studies. *Acceptability* measures include satisfaction with the online-streamed yoga intervention, perceived appropriateness of the intervention for this population, and intent to continue using intervention materials and will be assessed via satisfaction survey at post-intervention. *Demand*, including expressed interest in participating in study and actual use of intervention, will be measured via Udaya.com online tracking (i.e., # times logged in, time spent in class, completion of class, date/time of class access) and daily logs (i.e., yoga sessions, Borg Rating of Perceived Exertion Scale, and Meditative Movement Inventory). *Practicality* measures, including the ability of participants to carry out intervention activities (i.e., yoga), will be assessed via the Udaya.com tracking system, weekly logs, and satisfaction survey at the end of the intervention. *Qualitative interviews* following best practices for conducting interviews, including developing a priori questions and written moderator protocol and recording and transcribing data [61, 62], will be used to supplement information gained from the satisfaction surveys and to further understand the use of non-pharmacological interventions such as yoga in this population. Qualitative interviews will be administered in the intervention groups at post-intervention (12 weeks) and at follow-up (20 weeks).

For the intervention group(s), our benchmarks will be as follows: (1) feasibility (i.e., satisfaction, useful, appropriate, acceptable ≥70%, (2) demand (i.e., recommend to others, continue to use skills, program easy to complete ≥70%, and (3) attendance (i.e., at least 70% of participants in the moderate dose group will complete 150 min of yoga/week for at least nine of the 12 weeks (75%), at least 70% of participants in the low dose group will complete 60 min of yoga/week) for at least nine of the 12 weeks (75%). For the control group, our benchmarks will be as follows: (1) feasibility (i.e., satisfaction, appropriate, acceptable ≥70%) and (2) attendance (i.e., at least 70% of the control group will complete 60 min of stretching, toning, and limbering/week for at least nine of the 12 weeks (75%).

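### The sections give different release points for the video log-in, so the baseline accelerometer week may not be pre-exposure and the 12 attendance weeks have no fixed start

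*Protocol article*

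**What the plan says.** Three sections of the protocol article describe when a participant receives her log-in.

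- **Study enrollment, Phase 2.** Women complete the self-report baseline, and "Participants will then be randomized to an intervention (LD or MD) or control group". The packet, accelerometer and equipment are then posted. Women are asked to "begin wearing the GENEActiv immediately upon receiving it for one full week". Access comes after that: "When participants have worn the GENEActiv for 1 week, they will be emailed their UDAYA username and password to begin accessing their respective videos".
- **Allocation (phase 2 only).** "After randomization, participants will be emailed a study information packet (i.e., instructions, UDAYA username/password) according to the intervention assigned". The wear week is not mentioned, and the section adds: "The initiation of the study will begin after allocation to study arm".
- **Procedures.** Accounts are assigned on enrolment, and staff "will provide them with a username and password to access UDAYA prior to their participation in the study".

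Two other parts depend on this date. The later assessments are counted from baseline ("post-intervention (12 weeks from baseline) and follow-up (20 weeks from baseline"). The attendance benchmark in the Feasibility section asks for the weekly dose in at least nine of 12 weeks, stated as 75%, and does not say when week 1 begins.

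**The concern.** The accelerometer supplies the baseline measures of physical activity and objective sleep, yet it is posted only after randomisation, to women who may already know their arm. Holding back the log-in until the device week is over is the only stated safeguard that keeps that week free of study videos. If the log-in travels with the packet, or is given at enrolment, the safeguard is gone. A device week that already contains yoga or toning sessions cannot be repaired afterwards.

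The release date also decides how many weeks of access a woman has before the post-intervention visit. Attendance is one of the trial's feasibility benchmarks. Without a defined week 1, the same log-in records could be scored against different windows.

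**Working it through.** **Inputs from the protocol.** Intervention length, 12 weeks; benchmark, at least 9 weeks in at least 70% of participants; device wear, 1 week from receipt; visits at 12 and 20 weeks from baseline. **Assumed, because the protocol gives no figure:** mailing time m of 0, 1 or 2 weeks.

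**Step 1. The plan's own figure.** 9 / 12 = 75%, as stated.

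**Step 2. Gap between the release rules.** If the Allocation packet goes out promptly after randomisation, release after the wear week comes 7 days plus mailing time later. The 7 days come from the protocol; the mailing time does not.

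**Step 3. Weeks of access before the 12-week visit.** Take baseline as the self-report assessment, with randomisation soon after it. Under the Study enrollment rule, available weeks = 12 − 1 − m.

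| Mailing time m (assumed) | Weeks available | Nine weeks as a share |
|---|---|---|
| 0 | 11 | 9/11 = 82% |
| 1 | 10 | 9/10 = 90% |
| 2 | 9 | 9/9 = 100% |

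With prompt release after randomisation, close to 12 weeks remain and 75% holds.

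**Step 4. What this could do to the benchmark (illustration).** Assume independent weeks with the same completion probability p. For n available weeks, P(at least 9) = Σ C(n,k) p^k (1 − p)^(n−k), summed over k = 9 to n.

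| p (assumed) | n = 12 | n = 11 | n = 10 |
|---|---|---|---|
| 0.75 | 0.649 | 0.455 | 0.244 |
| 0.80 | 0.795 | 0.617 | 0.376 |
| 0.85 | 0.908 | 0.779 | 0.544 |
| 0.90 | 0.974 | 0.910 | 0.736 |

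Against the 70% target, the expected result changes sides at p = 0.80 when one week is lost and at p = 0.85 when two are lost. At 0.75 and 0.90 it stays on the same side throughout this table.

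**Step 5. If attendance is instead counted from first access for a full 12 weeks.** The benchmark stays at 75%, but those weeks end at week 1 + 12 = 13 or later after baseline. The 12-week visit then comes before the programme is complete. The gap from the end of the programme to follow-up is at most 20 − 13 = 7 weeks, rather than 20 − 12 = 8.

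**Step 6. Which baseline measures are exposed.** The self-report scales, including the IES-R, are completed before randomisation and so before any arm's videos can be assigned. Only the baseline accelerometer measures of activity and sleep follow randomisation.

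**The case against.** The best defence is that the timing can be reconciled. The Allocation section says only that the e-mail follows randomisation, and the end of the wear week also follows randomisation. The posted packet and the e-mailed packet could be two separate items, with the e-mail sent after the wear week. The Procedures wording fits release just before the videos start. Only Study enrollment gives an operational trigger, and that trigger protects the device week. The Timeline table also schedules a manual of procedures and staff training before recruitment.

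Much of this stands, and it is why the point is minor. It does not remove the difference in content: one section bundles the log-in with the instructions, while another separates it from the packet by a week of wear. Nor does it supply a start for the attendance weeks.

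Three stronger readings are tempting, and the document does not support them.

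- **Bias between arms.** The Blinding section gives the yoga arms and the control arm to different staff, so a reader might infer that the arms would follow different rules. Nothing says they would. Study enrollment describes one device procedure for all participants, and the ambiguity affects all three arms alike.
- **Half or more of the three-week allowance lost.** With 3 to 7 days of mailing assumed, the gap is 10 to 14 days, or 48% to 67% of three weeks. Counting that as lost attendance requires week 1 to run from randomisation while access waits for the wear week, and no section states that combination. With early release, the wear-week sessions could count; with late release and week 1 at access, nothing is lost.
- **No change from baseline in any arm.** This needs every woman to complete her full prescription during the device week. It also concerns prescribed minutes, which are not a listed outcome.

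**Conclusion.** The point holds as a minor inconsistency with two consequences. First, following the Allocation or Procedures section literally permits video use before or during the baseline device week, so baseline accelerometer activity and sleep may not be pre-exposure. The size of that effect cannot be derived from the document. The IES-R and the other self-report baselines are unaffected.

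Second, the attendance window is undefined. Release after the wear week leaves at most about 11 weeks of access before the 12-week visit, which makes nine weeks 82% or more of those available. This rests on two assumptions: that baseline means the self-report assessment, and that weeks are counted up to that visit. The 90% and 100% figures rest further on assumed mailing times, and the binomial figures on independent weeks and an assumed completion rate.

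**What to change.** Reconcile Procedures, Study enrollment and Allocation to one release point, identical in all three arms and after the baseline device week, as Study enrollment already states.

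- Take the log-in out of the packet described under Allocation, and align the Procedures sentence with it.
- Log the release date for each woman and count attendance week 1 from it.
- State what baseline means for the visit schedule and how the 12- and 20-week visits relate to the release date, so that the 12-week intervention is complete at the post-intervention assessment. Moving the attendance start alone would leave that visit too early.

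The cost is wording in three sections, a sentence on the visit anchor and one recorded date per participant. No extra visits, staff or measurements are needed.
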